### Sampling strategy

The study will utilize a consecutive sampling approach to recruit participants. This method involves selecting every eligible patient who meets the inclusion criteria and consents to participate until the required sample size is achieved. Once enrolled, participants will be randomly assigned to either Group A (intervention group) or Group B (control group) using a computer-generated randomization sequence.

This approach ensures that the sample accurately represents the diversity of the patient population typically seen in clinical settings while maintaining the practicality and efficiency needed in busy healthcare environments. The consecutive sampling aims to minimize the risk of selection bias, which may arise from convenience-based recruitment, while ensuring that enrollment strictly follows the eligibility criteria.

### Sampling procedure

The screening process will involve evaluating patients based on the predefined inclusion and exclusion criteria. This will include a review of medical records and an initial assessment to determine each patient’s eligibility for participation in the study. Once deemed eligible, patients will be approached consecutively and invited to participate. The recruitment process will continue until the required sample size is reached, ensuring that the study population is representative of the broader clinical population and diverse in terms of patient characteristics.

Before enrollment, written informed consent will be obtained from all participants. Patients will receive detailed information about the study, including its purpose, procedures, potential risks, and expected benefits. They will have the opportunity to ask questions before deciding whether to participate. Participation is entirely voluntary, and patients may withdraw from the study at any time without any impact on their standard medical care. After enrollment, participants will be assigned to one of the two study groups.

While contamination between groups is theoretically possible, it would likely lead to an underestimation of the intervention effect rather than an artificial inflation, as the intervention group receives all components provided to the control group plus additional materials. To mitigate this risk, participants were clearly instructed not to share training details or educational materials with others. Moreover, supplementary materials were distributed individually and not made publicly accessible, and educational sessions were scheduled to minimize overlap and patient interaction.

### Randomization and allocation concealment

A randomization list of 20 cases per center, allocated in a 1:1 ratio between the intervention (Group A) and control (Group B) arms, will be created using a simple randomization algorithm. Simple randomization was deemed appropriate for this study, given the limited number of patients, ranging from 4 to 20, expected to be enrolled at each center. Unlike block randomization, which could create challenges if a center fails to complete an entire block, simple randomization ensures flexibility while maintaining methodological rigor.

The randomization list will be generated independently by the methodologist responsible for the process, ensuring no bias or influence from investigators. This list will be securely stored and concealed from the principal investigator (PI) and study centers to maintain strict allocation concealment.

The randomization process will employ a sealed, opaque envelope system to ensure allocation concealment. For each center, 20 envelopes will be prepared, corresponding to the 20 cases on the randomization list. Each envelope will be sequentially numbered from 1 to 20 and will contain the group assignment (Group A or Group B) based on the randomization list. The envelopes will be opaque and sealed to prevent any possibility of visual identification of group assignments before opening.

Once prepared, the envelopes will be sent to each participating center in a tamper-proof package by the methodologist who created the randomization list. The randomization list will remain securely stored, ensuring that neither the PI nor the study sites have access to it. At each center, envelopes will be opened sequentially and in numerical order by a designated study coordinator after confirming the patient’s eligibility and obtaining written informed consent. The study coordinator will be trained to ensure compliance with the protocol and will have no involvement in delivering the intervention or assessing outcomes, maintaining a clear separation of roles and minimizing bias.

All randomization and allocation processes will be systematically documented. Once an envelope is opened, the group assignment will be recorded, and the envelope will be securely stored to maintain an audit trail. The randomization and envelope-opening processes will be periodically audited to ensure adherence to the protocol and to detect any deviations that may compromise allocation concealment.

### Sample size

The sample size for this study was determined to ensure sufficient statistical power to detect a meaningful difference in median I-CAT scores between the intervention and control groups. The primary endpoint aims to demonstrate an improvement in median I-CAT scores from 3.0 to 3.5, which corresponds to an increase from the median acceptance score to the 75th percentile of the previously reported distribution [10,11].

To achieve this, a significance level of 0.05 (5 %) was selected, meaning there is a 5 % probability of a Type I error, where a difference is incorrectly concluded when none exists. A power of 80 % (0.80) was chosen, ensuring that the study has an 80 % probability of detecting a true difference between the groups if one exists, thereby reducing the risk of a Type II error. Based on previous studies and pilot data, a standard deviation of 1 was assumed for the calculation [10,11]. Given these parameters, the sample size calculation was performed using a non-parametric (Mann-Whitney U) test to compare the two independent groups.

The formula used for calculating the required sample size accounts for effect size, significance level, and power. The required sample size per group, denoted as n, is calculated using the equation:(1)$$n=\frac{{\left(Z_{\alpha /2}+Z_{\beta }\right)}^{2}\times \;2\;\times \sigma^{2}}{\Delta^{2}}$$

In this approach, Z_α/2_ represents the Z-score for the chosen significance level (1.96 for α = 0.05), Z_β_ is the Z-score for the desired power (0.84 for 80 % power), σ² represents variance, and Δ is the effect size, defined as the difference between the 75th percentile and the median of the I-CAT score distribution. The calculations indicate that 64 participants per group are required to achieve the desired statistical power and significance level, resulting in a total sample size of 128 participants. This sample size is based on an effect size of 0.5, calculated as the difference between the two medians divided by the standard deviation. A sensitivity analysis was performed to evaluate how variations in the expected effect size impact the required sample size. For smaller effect sizes ranging from 0.5 to 0.2, the required sample size per group increased, ranging from 64 to 392 participants per group. Given the study objectives and feasibility considerations, the target sample size was determined, assuming an effect size of 0.5, confirming that 64 patients per group are sufficient to ensure reliable and statistically meaningful results.

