To evaluate the robustness of the findings, sensitivity analyses will be conducted, comparing the results of multiple imputations with alternative approaches, such as complete case analysis (where only participants with complete data are analyzed) and single imputation methods [18]. These analyses will ensure that the handling of missing data does not introduce bias into the study conclusions. The extent of missing data, the imputation methods applied, and the results of sensitivity analyses will be transparently reported in all study publications and presentations to ensure scientific integrity and reproducibility.

All statistical analyses will be performed using R (R Core Team, 2023). The significance level (alpha) for hypothesis testing will be set at 5 % (0.05). When multiple comparisons are conducted, appropriate adjustment procedures will be applied to control for Type I error inflation. Two-tailed tests will be employed for all analyses.

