## Protocol validation

Although no preliminary results are currently available, the hypothesis of a 0.5-point improvement in the I-CAT score at T2 is grounded in prior research and clinical reasoning. The assumption that the enhanced educational intervention will lead to a clinically meaningful increase in IC acceptance is supported by existing evidence on patient education and adherence to self-catheterization.

The I-CAT has been validated as a reliable measure of patient acceptance, with previous studies indicating that structured training and educational interventions significantly improve adherence and psychological comfort with IC [10]. The expected increase from a median I-CAT score of 3.0 to 3.5 represents a shift toward higher acceptance levels, aligning with improvements observed in studies evaluating similar patient-centered educational programs [20].

Moreover, previous research on adherence to self-catheterization suggests that educational reinforcement and patient-centered training approaches can lead to measurable improvements in acceptance and compliance [[21], [22], [23]]. The study design, which integrates a video tutorial and an informational booklet alongside standard training, is based on established methods that have been shown to enhance patient confidence, self-efficacy, and long-term adherence [24].

Additionally, the sensitivity analysis conducted during sample size estimation supports the feasibility of detecting this hypothesized effect. If the enhanced intervention successfully reduces negative perceptions and barriers associated with IC, a 0.5-point improvement in the median I-CAT score should be observable by T2.

The plausibility of this effect size is further reinforced by the structured follow-up assessments at T1 and T2, ensuring that the intervention’s impact on acceptance is tracked over time. Once data collection begins, adherence rates, patient-reported experiences, and I-CAT score distributions will provide further insights into the validity of the assumed effect size.

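### The sample-size inputs do not fit together under the normal-theory formula used, and the stated 80% power is not a figure for the planned Mann-Whitney test

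*Protocol article*

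**What the plan says.** The Sample size section of the protocol article sets the target as "an improvement in median I-CAT scores from 3.0 to 3.5" and says that this "corresponds to an increase from the median acceptance score to the 75th percentile of the previously reported distribution". The effect Δ in Equation (1) is defined as that same quartile gap. On the spread of the scores it says: "Based on previous studies and pilot data, a standard deviation of 1 was assumed for the calculation". The gap and the SD carry the same two references.

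The section reports that the calculation was made for a Mann-Whitney test, but Equation (1) is the usual formula for comparing two means. The result is 64 per group, 128 in total: "This sample size is based on an effect size of 0.5, calculated as the difference between the two medians divided by the standard deviation". For effect sizes from 0.5 down to 0.2, the section also reports 64 to 392 per group.

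The Primary endpoint section uses the shift from median to 75th percentile to argue clinical relevance, and repeats the 80% power. The Statistical plan section names Mann-Whitney for I-CAT at T2. The Protocol validation section opens: "Although no preliminary results are currently available".

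**The concern.** The sample size rests on one ratio, 0.5 divided by the SD. The numerator is a quartile gap and the denominator an SD, both attributed to the same published sources, so they should describe one distribution. Under the normal model usually paired with Equation (1), a quartile gap fixes the SD, and the value it fixes is not 1. If the score is not normal, the Mann-Whitney test's power depends on the shape of the distribution, which Equation (1) does not contain.

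What is at stake is how the result will be read. If the true power for a 0.5-point shift is about 96%, a null result is much stronger evidence against such a shift than the protocol implies. If it is in the low seventies, a null result is weaker evidence. The clinical reading of the target, a move from the median to the 75th percentile, depends on the same distribution.

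**Working it through.** **Inputs.** Two-sided α = 0.05 ("a significance level of 0.05 (5 %) was selected"; "Two-tailed tests will be employed for all analyses"), power 80% ("A power of 80 % (0.80) was chosen"), Δ = 3.5 − 3.0 = 0.5, SD = 1, allocation 1:1, Mann-Whitney test.

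**1. Reproducing the plan's figures.**
- Equation (1) at effect size 0.5: (1.96 + 0.84)² × 2 × 1² / 0.5² = 15.68 / 0.25 = 62.7, so 63 per group.
- Two-sample t-test at 0.5: 63.8, so 64 per group, with 80.1% power at 64.
- Equation (1) at 0.2: 15.68 / 0.04 = 392. The t-test gives 393.4, so 394.

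The stated range therefore starts with a t-test figure and ends with an Equation (1) figure. Neither is a Mann-Whitney figure.

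**2. Mann-Whitney, normal scores, SD 1.** Dividing the t-test size by the asymptotic relative efficiency 3/π (0.955) gives 63.8 × π/3 = 66.8, so 67 per group. Noether's formula gives 137 in total, so 69 per group. Simulated power at 64 per group is 78% to 79%.

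**3. The quartile gap under a normal model.** The 75th percentile lies 0.6745 SD above the median.
- Implied SD: 0.5 / 0.6745 = 0.741.
- Implied effect size: 0.5 / 0.741 = 0.67.
- Size for 80% power: 35 (Equation 1), 36 (t-test) or 38 (Mann-Whitney) per group.
- Power at 64 per group: 96.6% (t-test), about 96% (Mann-Whitney, simulated).
- Difference detectable with 80% power at 64 per group: 0.5 × 0.741 = 0.37 points.

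Conversely, with SD 1 the 75th percentile would be 3 + 0.6745 = 3.67, and a 0.5-point shift reaches Φ(0.5) = 0.69, the 69th percentile.

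**4. Non-normal shapes.** The article gives neither the range of the I-CAT nor its full distribution, so these shapes are assumptions. Each is piecewise uniform between the listed points, has median 3.0 and 75th percentile 3.5, and is shifted by 0.5 with the scale ceiling ignored. The comparison-of-means column is Φ(0.5 / (SD × √(2/64)) − 1.96).

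| Range; quartiles | SD | Comparison of means | Mann-Whitney, 64 per group (simulated) |
|---|---|---|---|
| 0–4; 2.5 / 3.0 / 3.5 | 1.01 | 80% | about 93% |
| 0.5–4; 2.0 / 3.0 / 3.5 | 0.98 | 82% | about 87% |
| 1–5; 2.0 / 3.0 / 3.5 | 1.05 | 77% | about 72% |

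The power for means stays near 80% while the Mann-Whitney power moves with the shape. Part of the shortfall in the last row comes from its SD of 1.05. Among shapes with an SD of exactly 1, the lowest power found was 76%. A right-skewed lognormal with exactly the three stated values exceeded 99%, so 93% is not a ceiling.

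**5. Source of the SD.** The Sample size section credits earlier studies and pilot data. No pilot is described anywhere in the article, and the Protocol validation section says that no preliminary results are available.

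**The case against.** The strongest reply is that nothing in the article says I-CAT scores are normal. Medians and a Mann-Whitney test suit a skewed score, and skewed distributions can have median 3.0, 75th percentile 3.5 and SD 1 together. Equation (1) needs only approximately normal sample means, so for a comparison of means the three inputs can coexist and still give about 80%. This stands. A reader might infer that the three values contradict each other outright, and the documents do not support that. The reply does not rescue the stated power, however, because the planned test does not compare means.

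A second reply is that 64 and 392 both reproduce, that the normal-model correction raises power, and that the downside is small. For a pure shift of a continuous score, the Mann-Whitney test's asymptotic efficiency against the t-test is never below 0.864, which leaves about 75% at SD 1. The sensitivity range and the Limitations section already allow for smaller effects: an SD of 1.25, for example, would be an effect size of 0.4. This also stands, and it is why enrolment need not change. A reader might infer that the trial is underpowered, but that is not shown.

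Third, a reader might take the Protocol validation section to say that the pilot data do not exist. It does not. The sentence concerns the hypothesis of a 0.5-point improvement, mentions neither a pilot nor the SD, and most naturally means that this trial has no results yet. What remains is that a pilot is invoked and never described.

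Finally, the cited sources are not at hand, so it cannot be checked which of the quoted values they report.

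**Conclusion.** The point holds in a limited form. Under the normal model, the quartile gap and SD 1 do not fit together: the gap implies SD 0.74 and about 96% power, while SD 1 removes the 75th-percentile reading of the target. Without normality they can fit, but the 80% is then not the power of the planned test, which ranged from about 72% to 93% over the tabulated shapes. Even in the most favourable case for the protocol's own inputs, normal data with SD 1, the 64 is a t-test size and Mann-Whitney power is 78% to 79%.

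These figures assume a pure 0.5-point shift and complete data on 64 per group. The non-normal shapes are illustrations, not estimates of the I-CAT distribution. The error could lie in either direction, and the documents do not show which. The unexplained pilot data are a minor matter of wording.

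**What to change.** Keep 128 patients.

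- Take the median, both quartiles and the SD from the cited I-CAT distribution and state them together in the Sample size section.
- Recompute the power of the Mann-Whitney test at 64 per group on that distribution, by simulation or through the probability that a Group A score exceeds a Group B score. Restate it in the Sample size and Primary endpoint sections with a range over plausible SDs and shapes.
- If the normal-theory calculation is kept instead, label it as such and choose one reading: keep SD 1 and drop the claim that 0.5 points reaches the 75th percentile, or keep the quartile gap and restate the effect size as about 0.67 with about 96% power.
- Say what the pilot data are, with their size and SD, and reconcile this with the Protocol validation section; otherwise delete the reference.

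The cost is a short recalculation and some rewording. Neither enrolment nor the primary analysis changes. The drawback for the authors is that the published power figure may go down as well as up.

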### Primary endpoint

The primary endpoint of this study is the improvement in median I-CAT scores at T2 (three months post-initial training), assessing IC acceptance. A 0.5-point increase in the median I-CAT score (from 3.0 to 3.5) represents a shift from the median to the 75th percentile of the previously reported distribution [10,11]. This reduction in IC-related reluctance is considered clinically meaningful, indicating a higher level of acceptance among participants receiving the enhanced educational intervention compared to those undergoing standard clinical practice training. The study is powered to detect this difference at T2, with 80 % power and a 5 % significance level, ensuring that the observed effect is both statistically and clinically significant.

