To further investigate factors associated with adherence and secondary outcomes, multivariable analyses will be performed. Logistic regression models will be used to analyze binary outcomes, such as adherence status, while linear regression models will be applied to continuous outcomes, including I-CAT scores. Predictor variables will include sociodemographic factors (e.g., age, education level, socioeconomic status), clinical characteristics (e.g., primary diagnosis, comorbidities), and intervention type (enhanced educational intervention vs. standard clinical training). Interaction terms will be incorporated to assess whether the effects of the intervention differ across subgroups, ensuring a comprehensive evaluation of potential effect modifiers. Model selection will be guided by theoretical considerations and statistical criteria, using stepwise or backward elimination methods to refine the models.

Handling missing data will be an important aspect of the analysis. This study assumes that data are missing at random (MAR), meaning that missingness is related to observed data but not to unobserved data [18]. All instances of missing data will be identified and documented, and patterns of missingness will be analyzed to determine whether they are systematically related to specific variables. Descriptive statistics will be used to summarize the extent and distribution of missing data for each variable.

Multiple imputation will be used as the primary method for handling missing data to minimize bias and preserve statistical power [19]. This approach generates multiple plausible datasets by imputing missing values based on observed data, which are then analyzed separately. The results from these datasets will be combined to produce estimates and confidence intervals that appropriately reflect the uncertainty introduced by missing data. Multiple imputations using chained equations will be performed, suitable for handling various variables, including continuous, binary, and categorical data.

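### The 64 per group is a t-test figure labelled as Mann-Whitney, and with no allowance for loss the stated 80% power at T2 applies only to complete follow-up

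*Protocol article*

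**What the plan says.** The Sample size section of the protocol article sets the target as "an improvement in median I-CAT scores from 3.0 to 3.5", with an assumed standard deviation of 1. On the error rates it says "a significance level of 0.05 (5 %) was selected" and "A power of 80 % (0.80) was chosen"; the Statistical plan adds "Two-tailed tests will be employed for all analyses". On method it says "the sample size calculation was performed using a non-parametric (Mann-Whitney U) test to compare the two independent groups". Equation (1) follows, and then the result: "The calculations indicate that 64 participants per group are required to achieve the desired statistical power and significance level", 128 in total. A sensitivity range of 64 to 392 per group is given for effect sizes from 0.5 down to 0.2.

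The Primary endpoint section repeats the claim: "The study is powered to detect this difference at T2", at 80% power and 5% significance. The Limitations section calls the sample size adequate for the primary outcome. Under Sampling procedure, recruitment runs until the required size is reached and patients may withdraw at any time. The Statistical plan names Mann-Whitney for I-CAT at T2 and says "Multiple imputation will be used as the primary method for handling missing data". It gives no expected rate of missing data.

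**The concern.** There are two separate problems. The first is that the named method and the printed formula differ: equation (1) has no term for a rank test, so a reader cannot tell which test the 80% belongs to. The second matters more. The number needed for analysis and the number to be enrolled are the same 128, in a trial that permits withdrawal and provides for missing data.

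The 80% is a figure that the trial relies on. It underlies the statement that 64 per group is sufficient and the later statement that the primary outcome is adequately powered. The Limitations section warns of low power only if the true effect is smaller than assumed. It does not mention lost T2 scores or the choice of test, so a null result could be read as stronger evidence against a 0.5-point effect than the trial can give.

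**Working it through.** **Inputs.** From Sample size and Statistical plan: two-sided alpha 0.05 (z = 1.96), power 0.80 (z = 0.84), difference 0.5, SD 1. From Study design: 1:1 allocation. Loss rates of 10, 15 and 20% are assumptions, because the article gives none.

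**1. The plan's own figures.**
- Equation (1), effect 0.5: (1.96 + 0.84)² × 2 × 1² / 0.5² = 7.84 × 2 / 0.25 = 62.72, so 63 per group.
- Equation (1), effect 0.2: 7.84 × 2 / 0.04 = 392.0, so 392 per group.
- Two-sample t-test (noncentral t): 63.8, so 64, and 393.4, so 394.

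The printed range of 64 to 392 therefore takes its first end from the t-test and its second from equation (1). The t-test power at 64 per group is 80.1%, so there is no margin.

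**2. The Mann-Whitney equivalent.** Divide the t-test number by the asymptotic relative efficiency, which is 3/π = 0.955 for normal data: 63.8 / 0.955 = 66.8, so 67, and 393.4 / 0.955 = 412. Noether's formula, with P(X<Y) = 0.638, gives 69 for the 0.5 effect.

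**3. Mann-Whitney power at 64 per group with complete data** (shift 0.5, SD 1; simulations of 20,000 trials per setting):
- normal scores: about 78% (78.3% by relative efficiency, 78.1% simulated)
- logistic scores: about 83%
- Laplace scores: about 91%

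The article also puts the 75th percentile 0.5 above the median. With SD 1 that gap is 0.67 for a normal, 0.61 for a logistic and 0.49 for a Laplace distribution. Taken together, the plan's SD and percentile point to tails heavier than normal.

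**4. Complete-case power after loss from 64 per group.** Evaluable n = 64 × (1 − loss), that is 57.6, 54.4 and 51.2.

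| Assumed T2 loss | t-test | Mann-Whitney, normal | Mann-Whitney, logistic | Mann-Whitney, Laplace (simulated) |
|---|---|---|---|---|
| 10% | 76% | 74% | 80% | 88% |
| 15% | 73% | 71% | 77% | 86% |
| 20% | 71% | 69% | 74% | 84% |

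The logistic value at 10% is 79.6% by relative efficiency and about 79% simulated, so it is at or just below the target.

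**5. Effect of baseline adjustment.** If the T0–T2 correlation is 0.4 (an assumption), the residual SD is √(1 − 0.4²) = 0.917 and the standardised effect is 0.5 / 0.917 = 0.546. With 54 per group, power is 80.2%.

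**The case against.** The strongest reply concerns the Mann-Whitney shortfall. A reader might infer that 64 per group simply fails to give 80% power for the named test. The documents do not support that. The shortfall appears if scores are normal, where it is about 2 points of power and 3 patients per group. The plan states no distribution, and its own SD and percentile fit heavier tails better, under which Mann-Whitney exceeds 80% with complete data. This part of the objection stands, and the shortfall must be stated as conditional on shape.

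A reader might also infer that the plan expects a particular amount of missing T2 data. It does not say so. It provides for missing data in general, gives no rate and does not single out T2. The loss rates above are illustrations. The lower powers are also complete-case values, while the primary method is multiple imputation with I-CAT available at T0 and T1. Imputation would recover power to the extent that those scores predict T2.

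The differences between 63 and 64, and between 392 and 394, change no decision by themselves. They matter only because they show which methods were used.

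Two things survive: the method is mislabelled, and nothing is added for loss. Neither depends on the score distribution. Nor can the second be put down to condensation for a journal, since the article prints the derivation, the total, the recruitment end point and the 80% claim.

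**Conclusion.** The point holds in a limited form. The calculation is a two-means calculation described as Mann-Whitney, and its sensitivity range joins two methods. The 64 reproduces as a t-test number with 80.1% power, and it serves as both the evaluable and the enrolled number. The 80% at T2 therefore applies to complete follow-up. At an assumed 10 to 20% loss, complete-case power falls to about 76–71% (t-test), 74–69% (Mann-Whitney, normal) or 80–74% (Mann-Whitney, logistic). Of the shapes examined at SD 1, only the clearly heavier-tailed Laplace stays above 80% throughout. All these figures rest on the plan's difference of 0.5 and SD of 1. The design is not invalidated, but the power statement should be corrected.

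**What to change.** In Sample size, name the method actually used and give the sensitivity range from one method: 63–392 by equation (1), 64–394 by t-test, or 67–412 by Mann-Whitney under normality. State the assumed score distribution and the expected T2 loss. In Sample size, Primary endpoint and Limitations, say that 80% power refers to 64 evaluable patients per group, and give the lower power at the expected loss. This is a change of wording and needs no extra enrolment; the cost is a less favourable power statement.

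Optionally, adjust the primary comparison for the T0 I-CAT score, which is already collected. Power would be about 80% at 54 per group (15% loss) if the T0–T2 correlation is 0.4, which the sponsor would need to support. The downside is that the primary test would no longer be a plain Mann-Whitney test, so the change should be made before any outcome data are seen by group.
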